### Blinding (masking)

Researchers collecting quantitative data will be blind to trial group allocation at baseline. After data collection and before intervention delivery, researchers will open an envelope to determine if the workplace is in the intervention group. Participants will not be told if they are in the intervention group. Some quantitative data collection will occur electronically, and this data collection mode does not involve researchers who are aware of the trial group.

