### Study design

The embedded mixed methods cluster randomised waitlist-controlled trial design will be realised with all participants being invited to attend two group sessions. The sessions will include both the data collection and intervention activities. The schedule of activities for these sessions is in Table 1. In Session 1 for the intervention group, they will receive a welcome, fill out the quantitative survey, have a general group discussion about health and wellbeing at work, and then receive the intervention (see below). Session 1 for the control group is identical except they do not receive the intervention. In Session 2, all participants will again receive a welcome and conduct a quantitative survey. The intervention group will then take part in a qualitative focus group about mechanisms, barriers, and enablers, whereas the control group will receive the intervention. Note that all surveys are carried out prior to discussion in both sessions, meaning endpoint measures will be taken from the control group before they receive their intervention.

**Table 1 pone.0282848.t001:** Schedule of activities for group sessions about health and wellbeing, which contain data collection and intervention activities.

**Session 1: Intervention group**	**Session 1: Control group**
a. Welcome	a. Welcome
b. Quantitative survey (baseline assessment)	b. Quantitative survey (baseline assessment)
c. Group discussion on health and wellbeing at work	c. Group discussion on health and wellbeing at work
d. Intervention	
**Session 2 *(4+wks after Session 1)*: Intervention group**	**Session 2 *(4+wks after Session 1)*: Control group**
a. Welcome	a. Welcome
b. Quantitative survey (endpoint assessment)	b. Quantitative survey (endpoint assessment)
c. Group discussion on mechanisms, barriers, enablers	c. Intervention

Note that the timing of activities with sessions corresponds with letters a-d (where a is first, b is second, etc.)

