### Interventions

#### Description of intervention

The intervention is mental contrasting plus implementation intentions. It will be delivered to employees from the same organisation in a group setting during working hours. The instructions that will be used to guide the delivery of the intervention and accompanying participant handout is enclosed in S3 File, which is derived from existing studies on mental contrasting and implementation intentions [32–34]. We enclose a more detailed description of the intervention in S4 File along with the completed TIDieR checklist [35]. In brief, all participants will be invited to attend a group session about health and wellbeing with other employees that lasts around one hour. All participants will be asked to think of something that they would like to do for their health and wellbeing (a ‘wish’) in the next four weeks that is important, achievable, and challenging. Part of the group session will contain the intervention activity (see Table 1). During the intervention activity, participants will be encouraged to use mental contrasting and implementation intention steps to reinforce the wish, turning it into a committed goal. Participants will also be provided with a handout that shows the steps and has space to practice using them.

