## Methods: Assignment of interventions (for controlled trials)

### Randomisation, allocation, sequence generation

All workplaces will be assigned an anonymous ID. An independent statistician will generate an allocation sequence using the random number generator in Stata v16.1 with assignments to the intervention or control group stratified by company size. Random block sizes of two and four will be used to maintain both balance within stratum and prevent lack of allocation concealment. A company will be considered small if there are less than 50 employees, medium is 51 to 250 employees and large is more than 250 employees [60]. The stratification variable was chosen based on a previous study [47]. The independent statistician will retain this list and it will be kept concealed from the study team. After baseline data collection has occurred in each workplace, its assignment will be revealed based on the next assignment in the sequence for its particular stratum.

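### Allocation may be revealed before the shared Session 1 discussion, and nothing shown requires the wish that defines the primary outcome to be recorded first

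*Protocol article*

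**What the plan says.** Two sections of the protocol article fix when allocation becomes known.

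- Randomisation, allocation, sequence generation: "After baseline data collection has occurred in each workplace, its assignment will be revealed based on the next assignment in the sequence".
- Blinding (masking): "After data collection and before intervention delivery, researchers will open an envelope to determine if the workplace is in the intervention group". The sentence before it limits the masking claim: "Researchers collecting quantitative data will be blind to trial group allocation at baseline".

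The Study design section and Table 1 give the order of Session 1. After the welcome (a), the intervention arm will "fill out the quantitative survey, have a general group discussion about health and wellbeing at work, and then receive the intervention"; these are steps (b), (c) and (d). For the other arm, "Session 1 for the control group is identical except they do not receive the intervention", so controls have steps (a) to (c) only. Table 1 describes step (c) as "Group discussion on health and wellbeing at work".

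The Description of intervention section says of the wish: "All participants will be asked to think of something that they would like to do for their health and wellbeing". It then gives the intervention activity a later role: "During the intervention activity, participants will be encouraged to use mental contrasting and implementation intention steps to reinforce the wish". Under Quantitative measures, the primary outcome is the participant's own rating, from 1 to 7, of progress on that wish, asked at endpoint.

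**The concern.** The primary outcome is rated against a target that each participant chooses in Session 1. If that target is chosen or shaped once the researchers know the arm, the yardstick can differ between arms for reasons unrelated to the intervention. Wishes might be easier, harder or vaguer in one arm. The shared discussion might also be led with more or less energy, or with more advice, for groups that will receive no exercise that day.

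Three features of the plan make this hard to repair in the analysis:

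- Progress is asked only at endpoint, so there is no baseline value to adjust for.
- The primary model contains the intervention indicator, the stratification covariate and a random effect for workplace. None of these reflects the difficulty or clarity of the wish.
- Participants who do not remember their wish are coded to the lowest point of the scale. How firmly the wish was elicited can therefore act on the outcome directly.

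All outcomes are self-reported, and participants are not told their arm. The conduct of the session leader is therefore one of the main routes by which knowledge of the arm could reach the data.

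**Working it through.** The plan gives no figure on this point, so the check sets the sections side by side. The power values in Table 2 describe sampling error and do not change under it.

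**1. Earliest permitted reveal.** The Randomisation section ties the reveal to the end of baseline data collection. Table 1 uses the baseline label for one step only, the survey (b). The Blinding section's upper limit is the start of the intervention (d). The permitted window therefore runs from the end of (b) to the start of (d), and the whole of (c) lies inside it. Opening the envelope between (b) and (c) complies with both sections. So does opening it between (c) and (d).

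**2. What is masked.** The masking statement covers researchers while they collect baseline quantitative data. It covers neither the discussion nor the elicitation of the wish.

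**3. When the wish is set.** Both arms are asked for a wish, and the intervention activity reinforces one that already exists. Controls have only (a), (b) and (c) in Session 1, so by elimination their wish is set in one of these:

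| Step at which the wish is elicited | Possible order relative to the reveal |
|---|---|
| (a) welcome | before the reveal under either section |
| (b) survey | before the reveal under either section |
| (c) discussion | after the reveal, if the envelope is opened straight after (b) |

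No section shown says which row applies. The summary of survey content under Quantitative measures names no item that asks for the wish, which leaves (c) plausible. The questionnaire (S9 File), the delivery instructions (S3 File) and the fuller intervention description (S4 File) are not shown, so (a) and (b) remain open.

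**4. Is the wish protected by rule?** No section shown says that the wish must be recorded before the envelope is opened.

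**5. Result.** The stated rule allows the arm to be known throughout the shared discussion. If wishes are elicited in that discussion, it also allows the arm to be known when the wish is chosen. The first follows from the text. The second depends on a step that the article does not state.

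**The case against.** The strongest reply is that data collection in the envelope sentence may include the discussion. The Study design section divides session content into data collection and intervention activities, and the discussion is not the intervention. The Qualitative measures section adds that all groups answer general questions about health at work, which matches the topic of step (c). The envelope sentence, unlike the one before it, does not restrict itself to quantitative data. On this reading the envelope is opened between (c) and (d), and the problem is already handled. The reading is reasonable, but the Randomisation section speaks of baseline data collection and Table 1 reserves that label for the survey. The text allows both readings.

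A reader might infer more than the article supports:

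- *That controls have to choose their wish in the discussion with the arm already known.* No section places wish selection there. If the wish is set in the welcome or the survey, it precedes any reveal.
- *That the person who opens the envelope leads the discussion.* The Intervention delivery section says who delivers the intervention. It does not say who leads step (c).
- *That the plan contradicts its description of Session 1 as identical in the two arms.* That sentence describes planned content and makes no claim about masking. The limitations section concedes that blinding is not fully possible.

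It can also be said that the exact moment of opening an envelope belongs in a session script. That would hold if the article were silent. It states a rule in two sections, and the rule as stated leaves the gap.

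**Conclusion.** The point holds in a limited form. The reveal rule permits allocation to be known before the shared discussion, and nothing shown requires the wish behind the primary outcome to be recorded before the reveal. The plan therefore does not exclude influence by arm-aware researchers on the discussion or, if wishes are elicited there, on the choice of wish.

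The size and direction of any bias cannot be derived from the document. The half-point target difference is the only yardstick available, and setting a bias against it would need an assumed shift for which the article gives no basis. The document does not show that bias will occur or that wishes are chosen after the reveal.

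The conclusion rests on reading the baseline label as Table 1 uses it, and on the shown text alone. If S3, S4 or S9 places the wish in the welcome or the survey, the exposure of the wish disappears and only that of the discussion remains. If data collection is meant to include the discussion, the intended practice is already sound and only the wording needs attention. This is a free improvement and not a flaw that threatens the trial.

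**What to change.** In both the Randomisation and the Blinding sections, replace the window with a fixed point: in both arms, every participant's wish is recorded and step (c) is finished before the envelope is opened, immediately before step (d). In control workplaces the envelope is opened at the same moment, where step (d) would otherwise begin. Name in Table 1 the step at which the wish is elicited, and align the session script with it.

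The cost is a sentence in each section and a fixed order in the script. No additional participants, visits or analyses are needed. If wishes are not yet written down in Session 1, recording them adds the same brief step to both arms.

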## Methods: Data collection, management, and analysis

### Data collection methods

Quantitative data collection will occur immediately before and at least four weeks after the intervention (see Table 1 and S7 File). Data collection will be conducted virtually (using Qualtrics e-surveys), face-to-face (via pen/pencil and paper), or over the phone (with researchers inputting participants’ responses into Qualtrics e-surveys), depending on the preferences of the workplaces and their staff. Qualitative data about the intervention will be collected in Session 2 (see Table 1 and S7 File), after quantitative endpoint data collection and at least four weeks after the intervention. We anticipate collecting qualitative data via virtual focus groups (unless another mode is preferred), and quantitative data via online e-surveys at the beginning of the focus groups. If participants are not able to attend their second session, they may be emailed a link to the e-survey or called to complete it over the phone. The e-survey questionnaire is in S9 File, and the qualitative focus group discussion guide is in S6 File. Sessions, including the data collection tools, will be piloted with an organisation not in the trial.

### Data management

Qualitative recordings will initially be stored on the Cloud of [anonymous for peer review] associated with Zoom or Microsoft Teams. Recordings may also be made in password-protected handheld recording devices. All interview links will be password-protected. Data from quantitative online interviews will be exported from Qualtrics survey platforms and stored on secure [anonymous for peer review] servers. Quality checks will be performed on the quantitative data, including checking for the proportion of missing data and plausible values.

### Analysis of quantitative data (statistical methods)

All analyses will be intention to treat, meaning that workplaces (clusters) will be analysed according to their randomisation allocation. Baseline characteristics will be summarised by intervention and control group. Means and standard deviations or medians and interquartile ranges will be used to summarise numeric characteristics, as appropriate. Frequencies and percentages will be used to summarise categorical characteristics. A flowchart will be created to show the flow of the workplaces and employees throughout the trial.

The primary comparison will be between clusters randomised to the mental contrasting intervention versus clusters randomised to the control. For the primary outcome, whether an employee has made any progress towards their wish (measured on seven-point scale), a Bayesian mixed effects linear regression model will be fitted to calculate the mean difference between the intervention and control group. Any participants who did not remember their wish will be coded into the lowest point category. Assumptions for linear regression will be checked and data transformations will be considered if necessary. The model will include an intervention indicator, covariate used in the randomisation (cluster size) and cluster as a random effects term. A Bayesian approach will be used for the incorporation of prior uncertainty, assigning “uninformative vague” prior distributions to the model parameters with a mean of 0 and a standard deviation of 10,000. For the primary analysis, observations with missing outcome data will be excluded.

Additionally, secondary analysis will be completed fitting a fully adjusted model for the primary outcome which will adjust for the following covariates: gender; household income; ethnicity; disability; self-rated health; occupational role (professional versus non-professional [61], see questionnaire in S9 File); home working; health risks; duration in job role and organisation size. Multiple imputation will be completed if there is more than five percent missing covariate data [62]. Multiple imputation will allow for the clustered nature of the data and the number of imputations will be dependent on the percentage of missing data.

All other secondary outcomes are on a similar or same scale to the primary outcome and therefore will take the same format as the analysis above. For secondary outcomes such as self-reported health, models will have an indicator for baseline or endpoint measures.

Subgroup analysis will be completed for the primary outcome by workplace and demographic characteristics, using interactions tests. Demographic and workforce characteristics will include gender (male/female/other), household income (less than 10K, 10-20K, 20-30K, 30-40K, 40-50K, 50-60K, 60-70K, 70K+), ethnicity (White; Mixed or Multiple Ethnic Groups; Asian or Asian British; Black, Black British, Caribbean or African, Other, Prefer not to state), disability (yes ‐ specify, no), self-rated health (poor, fair, good, very good, excellent), occupational role, home worker, health risks at work (“I feel physically safe at work?” completely agree, mostly agree, slightly agree, slightly disagree, mostly disagree, completely disagree), duration in job role (less than six months, six months to a year, more than a year) and organisation size (small, medium, large).

All estimates will be reported with 95% credible intervals and posterior probabilities for any benefit will be reported (mean difference>0). All analyses will be completed in Stata v16.1**.**

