Our quantitative measures were informed by a meeting with researchers, the local government team, and PPI representatives using guidance from the What Works Centre for Wellbeing on modelling the relationships between individual and community wellbeing. This guidance focusses attention on different levels of individual and workplace communities, including unintended outcomes and sub-group differences [46]. We also drew on a logic model from prior research with the local government team [47], modified and shown as a causal chain in a diagram S5 File. In line with theory on causal reasoning, we show our quantitative observations across a causal chain going from the intervention to employees’ perceived empowerment to change their health and wellbeing, employee perceptions of progress towards their health and wellbeing goals, employee behaviour change, and subjective wellbeing [48]. Note that employee behaviour change and wellbeing may occur as a result of largely automatic and unconscious attentional processes, bypassing conscious perception, which the diagram reflects [49, 50].

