### Sample size

A sample size of 60 workplaces is planned to participate in the trial based on what the local government team have stated as feasible, they will be allocated equally between the intervention and control group. Data from a previous cluster randomised trial [56] that included 100 workplaces was used for the estimating average cluster sizes and the coefficient of variation of cluster sizes. Data from a previous study [36] with a similar outcome was used to calculate the standard deviation of the outcome. No data or published trial results were available from which to estimate or inform intra-cluster correlations coefficients (ICCs), so in place as recommended we have used a range of plausible values [57].

Our sample size calculation is based on the main continuous outcome (how much progress towards goal achievement, measured on a seven-point scale), a parallel cross-sectional design, an exchangeable correlation structure, an average cluster size of 10, varying cluster size (coefficient of variation: 0.30), likely estimates of the ICCs (0.01, 0.05, 0.10) and a standard deviation of 1.55 in the progress towards achievement scale implemented using design inflation factors for the cluster randomised nature of the design [58]. Over 80% power is available across all scenarios to detect a half-point increase in the outcome between the intervention and control group (see Table 2). A difference of a half-point was considered clinically important because it can be difficult to change health behaviours even when people intend to make a change [59].

**Table 2 pone.0282848.t002:** Power achievable under anticipated available sample size over plausible scenarios.

Mean difference	ICC = 0.01	ICC = 0.05	ICC = 0.10
1	1.00	1.00	1.00
0.5	0.96	0.90	0.80
0.25	0.47	0.37	0.29

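### The primary model is valid but uses no individual baseline covariate; adding a short fixed list of pre-allocation baseline values would gain some precision at almost no cost

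*Protocol article*

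**What the plan says.** The section on analysis of quantitative data fixes the primary model: "The model will include an intervention indicator, covariate used in the randomisation (cluster size) and cluster as a random effects term". The Randomisation section shows that the stratification covariate is company size.

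The next paragraph of the analysis section adds that "secondary analysis will be completed fitting a fully adjusted model for the primary outcome". Its covariates are gender, household income, ethnicity, disability, self-rated health, occupational role, home working, health risks, job duration and organisation size. Clustered multiple imputation applies if more than 5% of covariate data are missing. Baseline empowerment and mental wellbeing are not on the list.

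Table 1 (Study design) gives both arms a baseline survey in Session 1, before discussion or intervention. The Randomisation and Blinding sections say that a workplace's allocation is revealed only after its baseline data are collected.

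The primary outcome, progress towards a self-chosen wish, is asked at endpoint. No baseline value of it is described. The sample size section accordingly assumes "a parallel cross-sectional design, an exchangeable correlation structure".

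**The concern.** Baseline values recorded before allocation is known cannot be affected by the arm, so they are safe covariates. If they predict the outcome, including them narrows the interval for the treatment effect and corrects the estimate for chance differences in participant mix. Stratification controls company size only.

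Precision matters here. Power at the largest ICC considered is only just 0.80. The Recruitment section puts the number of organisations in the initiative at approximately 60, and the plan uses 60, so the trial has little room to grow. Baseline adjustment is one of the few ways left to improve precision.

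The secondary adjusted model does not serve this purpose well. The Quantitative measures section says its demographic and workplace items were collected to capture diversity and assess inequalities. Several have many categories: as listed for the subgroup analyses, income has eight, ethnicity six, physical safety at work six and self-rated health five. A short list chosen for prognostic value would be a different and leaner model.

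**Working it through.** **Inputs from the Sample size section.** "A sample size of 60 workplaces is planned to participate in the trial", split equally, so 30 per arm. For clustering, the section uses "an average cluster size of 10, varying cluster size (coefficient of variation: 0.30), likely estimates of the ICCs (0.01, 0.05, 0.10"). The outcome SD is 1.55 and the target difference is 0.5 points. Two-sided alpha of 0.05 is assumed because none is stated.

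**Step 1: reproduce Table 2 without covariates.**

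Design effect = 1 + ((1 + CV²) × m − 1) × ICC, where (1 + 0.09) × 10 − 1 = 9.9.

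SE = 1.55 × √(2 × design effect / 300), and power = Φ(0.5/SE − 1.96).

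| ICC | Design effect | Effective n per arm | Power, recomputed | Power, Table 2 |
|---|---|---|---|---|
| 0.01 | 1.099 | 273.0 | 0.965 | 0.96 |
| 0.05 | 1.495 | 200.7 | 0.898 | 0.90 |
| 0.10 | 1.990 | 150.8 | 0.800 | 0.80 |

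The stated power is reproduced, so it does not depend on baseline adjustment. At ICC 0.10 the SE is 1.55 × √(2 × 1.990/300) = 0.1785, and power is 0.7997 before rounding. A t reference with 58 degrees of freedom gives 0.786.

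**Step 2: add baseline covariates.** The documents give no R², so 0.05 to 0.15 is an assumption. Two cases bracket how the explained variance might be distributed.

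- *Both levels:* R² applies equally within and between workplaces, so SE = 0.1785 × √(1 − R²).
- *Within workplaces only:* the design effect of 1.990 is replaced by (1 − 0.10)(1 − R²) + 0.10 + 9.9 × 0.10 = 1.990 − 0.90 × R². For R² = 0.10 this is 1.900, so SE = 1.55 × √(2 × 1.900/300) = 0.1744.

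| R² (assumed) | Power at ICC 0.10, within only | Power at ICC 0.10, both levels |
|---|---|---|
| 0 | 0.800 | 0.800 |
| 0.01 | 0.802 | 0.804 |
| 0.05 | 0.809 | 0.819 |
| 0.10 | 0.818 | 0.839 |
| 0.15 | 0.827 | 0.859 |

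The within-only case gains less because adjustment leaves the between-workplace part of the variance untouched. At the smaller ICCs there is less to gain: with R² = 0.10 at both levels, power goes from 0.965 to 0.978 at ICC 0.01 and from 0.898 to 0.926 at ICC 0.05.

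**Step 3: size of a chance imbalance.** For a covariate with ICC 0.05 (assumption), the between-arm difference in means has SD √(2/300 × 1.495) = 0.0998 covariate SDs. With a correlation of 0.3 to the outcome (assumption), this is 0.3 × 1.55 × 0.0998 = 0.046 points. That is under a tenth of the half-point target and about a quarter of the SE (0.046/0.1785 = 0.26).

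**The case against.** The strongest reply is that nothing here is wrong. A mixed model with arm, stratifier and random workplace effect is valid, and it matches the cross-sectional basis of the power calculation. That stands. A reader might infer from the missing covariates that the primary analysis is biased or underpowered against its own plan. The documents do not support this: Table 2 is reproduced without covariates, and power is 0.90 or more at the two smaller ICCs.

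Nor is adjustment abandoned, as a reader might also conclude. The same primary outcome has a prespecified adjusted model that includes self-rated health. What remains open is which model is primary and whether its covariates are the useful ones.

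Prognostic value is not shown either. The Quantitative measures section describes a chain from the intervention through empowerment to "employee perceptions of progress towards their health and wellbeing goals". In that chain empowerment responds to the intervention. It does not follow that baseline empowerment predicts progress towards a self-chosen wish. With no baseline value of the outcome, the usual strong covariate is missing. This stands, and it is why only modest R² values are used.

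Baseline collection of empowerment and mental wellbeing is likely but inferred. The article names self-reported health as an example of an outcome measured at both times, and the questionnaire is in a supplement not shown here. The fix has to be conditional on this.

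It is also tempting to count chance imbalance as a second harm. It is not bias: the unadjusted interval already allows for it, and removing it is the same benefit as the precision gain.

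**Conclusion.** The point holds as an efficiency recommendation. The primary model is sound but leaves baseline information unused, and the secondary adjusted model is not built to exploit that information. At ICC 0.10 the gain for a half-point difference is about 1 to 3 percentage points of power if the covariates explain only within-workplace variance, and about 2 to 6 points if they explain variance equally at both levels. Both ranges assume R² of 0.05 to 0.15, two-sided alpha of 0.05 and the plan's own SD, cluster size and coefficient of variation. The documents cannot settle R²; at 0.01 the gain is under half a point.

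**What to change.** Before any outcome data are seen by arm, amend the primary model to include a short, fixed list of values collected before allocation is revealed:

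- baseline self-rated health;
- the empowerment and short mental wellbeing measures, if the questionnaire confirms that they are taken at baseline.

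Keep the company-size stratum and the random workplace effect. Report the current model as a sensitivity analysis. Fill the few missing baseline values by simple imputation, so that no participant with an outcome is lost. If the team prefers the present model as primary, one line explaining why adjustment is secondary would be enough.

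The cost is about a sentence in the analysis section and no new data. The article describes empowerment only as several adapted measures, so its scoring must be defined in advance, together with the rule for missing covariates.

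### For secondary outcomes measured at both sessions, the listed model terms, read literally, make the intervention coefficient about half the endpoint effect, and the plan does not say which coefficient is the effect

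*Protocol article*

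**What the plan says.** The section on analysis of quantitative data in the protocol article first sets out the model for the primary outcome: "The model will include an intervention indicator, covariate used in the randomisation (cluster size) and cluster as a random effects term". The randomisation section shows that the covariate meant is the company-size stratum. The remaining secondary outcomes "therefore will take the same format as the analysis above". For those measured twice there is one further sentence: "For secondary outcomes such as self-reported health, models will have an indicator for baseline or endpoint measures".

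Interactions are named in one place only: "Subgroup analysis will be completed for the primary outcome by workplace and demographic characteristics, using interactions tests". The section does not say how the intervention indicator is coded when there are two time points, or which coefficient will carry the credible interval and the posterior probability of benefit.

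Two statements elsewhere fix what the data will look like. On baseline, the randomisation section says: "After baseline data collection has occurred in each workplace, its assignment will be revealed". On the endpoint, the study design section says that "endpoint measures will be taken from the control group before they receive their intervention". Table 1 shows the survey at both sessions in both groups.

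**The concern.** The intervention indicator is defined for an outcome asked only at endpoint, in an analysis by randomised allocation. There it can only mean arm. When the same format is carried over to data with a baseline row and an endpoint row per person, an arm term plus a time term fits a single arm difference to both sessions. Randomisation makes that difference zero in expectation at baseline, so the fitted value is pulled towards zero.

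At stake are the estimates for self-rated health, empowerment and psychological wellbeing, which make up much of research question 2. An analyst who followed the listed terms literally would report an attenuated effect with a credible interval centred in the wrong place. A second analyst who coded the indicator differently would report an effect twice as large from the same data and the same text.

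**Working it through.** **Inputs from the protocol article.** From the sample size section: 60 workplaces, 30 per arm; average cluster size 10; coefficient of variation 0.30; ICC 0.01, 0.05 or 0.10; SD 1.55; target difference 0.5 (the last two are for the primary outcome). The model terms and the timing of the measurements are as set out above.

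**Assumed, not in the document.** Endpoint loss of 0, 20 or 40%, equal in both arms. Half of the within-workplace variance is stable within a person (main simulation). For the coverage figures, an effect of 0.30 SD and a within-person correlation of 0.6.

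**1. The plan's own figure.** Table 2 concerns the primary outcome; no figure is given for the model at issue. It serves to check the inputs.

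- Design effect = 1 + ((1 + 0.30²) × 10 − 1) × ICC = 1 + 9.9 × ICC, giving 1.099, 1.495 and 1.99.
- Effective number per arm = 300 / design effect = 273.0, 200.7 and 150.8.
- Power = Φ(0.5 / SE − 1.96), with SE = 1.55 × √(2 / effective number) and a two-sided 5% level assumed. This gives 0.965, 0.898 and 0.800, against 0.96, 0.90 and 0.80 in Table 2.
- For a difference of 0.25: 0.470, 0.365 and 0.288, against 0.47, 0.37 and 0.29.

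Table 2 reproduces.

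**2. What the arm coefficient estimates.** Let d be the endpoint effect and τ the change over time without intervention. The expected means are:

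| | Baseline | Endpoint |
|---|---|---|
| Control | μ | μ + τ |
| Intervention | μ | μ + τ + d |

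An additive arm + time model fits one arm gap to both columns. With n0 baseline rows and n1 endpoint rows per arm, that gap is

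(n0 × 0 + n1 × d) / (n0 + n1).

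- No loss: 300d / 600 = 0.50d.
- 20% loss: 240d / 540 = 0.44d.
- 40% loss: 180d / 480 = 0.375d.

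The workplace random effect does not rescue this, because arm is constant within a workplace.

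**3. Other codings of the same data.** If the indicator is 1 only for intervention workplaces at endpoint, then μ + τ × time + d × indicator reproduces all four means exactly and the coefficient is d. Adding an arm-by-time term to arm + time also recovers d, as the interaction coefficient.

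**4. Simulation.** 60 workplaces, true d = 0.5, SD 1.55, 150 runs per row, linear mixed models with a workplace random intercept. Mean estimates:

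| Endpoint loss | ICC | Arm + time: arm | Endpoint-only indicator + time | Arm + time + interaction: interaction |
|---|---|---|---|---|
| 0% | 0.01 | 0.239 | 0.486 | 0.491 |
| 0% | 0.10 | 0.248 | 0.494 | 0.493 |
| 20% | 0.01 | 0.226 | 0.501 | 0.497 |
| 20% | 0.10 | 0.228 | 0.504 | 0.499 |
| 40% | 0.01 | 0.179 | 0.494 | 0.498 |
| 40% | 0.10 | 0.195 | 0.495 | 0.491 |

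Monte Carlo standard errors are 0.009 to 0.015. The arm coefficient is 0.48 to 0.50 of d with no loss, 0.45 to 0.46 with 20% loss and 0.36 to 0.39 with 40% loss, in line with step 2.

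**5. Effect on the interval.** With ICC 0.05, a true effect of 0.30 SD and a within-person correlation of 0.6, two separate simulations (300 and 120 runs) gave:

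- arm + time: mean 0.153 and 0.145; the 95% interval covered the true effect in 62% and 59% of runs and excluded zero in 38% and 34%;
- endpoint on arm and baseline value: mean 0.306 and 0.301; coverage 96% in both; zero excluded in nearly 100% and in 98%.

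The mixed models in steps 4 and 5 are not the planned Bayesian fit. With priors as vague as those stated, the estimates should be close.

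**The case against.** The best reply is that the halving is inferred from silence in a condensed article. The sentence does not say that the time indicator enters only as a main effect, it does not define the intervention term at two time points, and it does not exclude an interaction. An indicator coded 1 only for intervention workplaces at endpoint fits the listed terms and is unbiased. The care taken to survey controls before their intervention suggests that an endpoint contrast is intended. All of this stands, and it makes the bias conditional on coding. It does not dispose of the point: the sentence was written for outcomes measured twice, the indicator is carried over from a model in which it can only be arm, and following the listed terms gives a wrong estimate.

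A reader might infer more than the document supports:

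- **That the plan certainly halves these effects.** It does so on the literal reading, not on every reading.
- **That all of research question 2, or the primary result, is affected.** The progress item and the behaviour-progress item ask at endpoint about progress on the wish and have no baseline.
- **That power falls to the 0.25 row of Table 2.** That table is for an endpoint-only comparison of the primary outcome, and the stacked model has a different standard error.
- **That omitting a participant random effect is itself an error.** This rests on silence alone, and its size depends on assumptions. For an interaction model without that term, the simulated model standard error was 0.111 against a true SD of about 0.070. That true SD supposes workplace effects identical at both sessions: √(2 × (0.8/10) / 30) = 0.073. If workplace effects correlate 0.5 over time, it is √(2 × (0.05 + 0.75/10) / 30) = 0.091, and the gap narrows.
- **That the baseline data are wasted.** Under endpoint-only coding or an interaction they do contribute to the estimate.

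**Conclusion.** The point holds in conditional form. For secondary outcomes measured at both sessions, the protocol article lists arm, size, workplace and a time indicator, and leaves the effect coefficient undefined. With the indicator read as randomised arm and no interaction, the coefficient is 0.50 of the endpoint effect with complete data and 0.44 under an assumed 20% endpoint loss. This ratio needs only a zero expected baseline difference and equal loss in the arms; it does not depend on the ICC, the SD or the effect size.

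The coverage of about 60% and the figures for excluding zero are less firm. They rest on the assumed 0.30 SD effect and within-person correlation of 0.6, neither of which is given for these outcomes, and undercoverage would be milder for smaller effects.

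This should be fixed before analysis. It is not critical to the trial, because only secondary outcomes are involved.

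**What to change.** State that, for each outcome collected at both sessions, the endpoint value will be modelled on randomised arm, the baseline value of that outcome, the organisation-size stratum and a workplace random effect, and that the arm coefficient is the reported effect. This removes the ambiguity over coding and uses the baseline values already collected.

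An acceptable equivalent is a longitudinal model with a common baseline mean in the two arms, an arm contrast at endpoint, and workplace and participant random effects, with the endpoint contrast named as the reported effect.

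Either costs a sentence or two of analysis text and needs no new data. The analysis of the primary outcome and of the behaviour-progress item stays as it is.
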